#### Echocardiography

Usual and additional echocardiographic measures, such as volumetric gradients and diastolic parameters, will be analyzed in the selection of eligible patients (ejection fraction calculated by Teichholz method, ≥ 50%) [16] and after intervention by using two-dimensional echocardiograms (Philips IEE 33).

### Randomization

Patients who meet the eligibility criteria will be invited to participate in the study; those who accept to participate will sign a written informed consent form. Following the conclusion of pre-intervention tests, the researcher will inform the biostatistics center at HCPA, which is in charge of the randomization list, and participants will be allocated to either yoga (active) or yoga (passive) or control group in a 1:1:1 ratio using a pre-generated simple randomization list.

### Sociodemographic and clinical variables

A structured questionnaire will be filled by all study participants to collect sociodemographic data and clinical parameters (age, sex, education, current occupation or previous occupation when retired, daily routine, etiology and HF duration, presence of comorbidities such as hypertension, atrial fibrillation and aortic or mitral valve disease, history of smoking and alcohol intake, medications, hospitalizations, previous illnesses, presence of angina, stent placements, history of acute myocardial infarction, NYHA functional class, echocardiographic data). Weight, height, body mass index [28], vital signs, and electrocardiogram at rest will be evaluated in the first and last CPET.

Patients should be instructed to maintain their activities of daily living and eating routine, as established on the date of enrollment. Any change in pharmacological management should also be reported and recorded in the study.

### Endpoints

The primary endpoints are inspiratory muscle strength by measuring maximal inspiratory pressure (PI_max_).

Secondary endpoints include (1) vagal activity in resting and exercising (HRV); (2) peak VO_2_; (3) QoL Minnesota scores as a specific inventory for patients with HF; (4) functional capacity (NYHA Classification); (5) volumetric ratios of left atrial and diastolic pressure gradients on echocardiography; and (6) changes in BNP/NT-proBNP tests between pre- and post-intervention measurements.

### Independent/exposure variables and confounding

In both intervention groups (Active breathing technique or Passive breathing technique) the main independent variable includes respiratory management with different rhythms.

The effect of each intervention over the trial endpoints must be controlled for the confounders of concomitant physical exercise or co-intervention, and any changes regarding medications or non-pharmacological treatment.

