## Methods/design

### Study design

A PROBE (prospective randomized open blinded end-point) parallel-group trial with three groups will be conducted at two specialized HF clinics (HF Clinic at Hospital de Clínicas de Porto Alegre (HCPA), RS, Brazil, and the HF ambulatory at Hospital ULBRA-Mãe de Deus, Canoas, RS, Brazil). The researchers will be divided according to their specific role in this study as (1) interveners – those performing the protocol interventions (blinded for outcomes, but not for groups); (2) medical appraiser – responsible for performing clinical tests (blinded for groups, but not for outcomes); and (3) analysts – those responsible for the statistical analyses (blinded for both groups and outcomes). The individuals will be instructed to avoid talking with the research team about protocol intervention and clinical trials.

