#### Yoga – active breathing technique

Active protocol with yoga body movements (*àsanas*) performed along with respiratory technique without contentions, current and vigorous (*ujjayi*), observing a respiratory frequency of 15–20 respiratory cycles per minute. This session should last around 45 min.

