#### Control group (standard pharmacological treatment)

Patients will be oriented to keep their pharmacological routine and daily activities with no structured exercises. They will have to return to the hospital for post-testing after 8 weeks of randomization. After final assessment, all patients, including those in the control group, will be invited to participate in the study breathing activities at the outpatient wards of this trial.

Intervention will last 8 weeks (16 sessions). The post-intervention tests will be performed at the end of the intervention period for the evaluation of endpoints (Fig. 2). To ensure security, data will be stored both in the main researcher’s and study coordinator’s computers, as well as being added to a virtual drive. Researchers, study coordinators, doctors, and statisticians will be allowed data access. Interventions will occur at specific facilities in HCPA (physiatrist sector) and in ULBRA University hospital (medical school) according to patient enrollment. Protocol deviation and adverse events involving individual participants in clinical studies in the HCPA are recorded in the strategic adviser system available in the hospital intranet. Deviations and adverse events occurring at ULBRA will be recorded in the same system as the HCPA. The auditing procedures will occur randomly or designated by the ethical committee for research analysis.

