### Statistical analysis

Initially, a descriptive analysis will be performed and data will be expressed as absolute and relative frequency, besides mean and standard deviation or quartiles, accordingly. The treatment groups will be compared using the generalized estimating equation, specific for repeated measurements, in order to compare the effects (means) across the three groups and the two times, in addition to the group × time interaction. The generalized estimating equation matrix of robust estimator covariance and exchangeable work correlation matrix will be used if normal distribution is found and will be analyzed by an identity binding function. In contrast, if an asymmetrical distribution is found, data will be analyzed using a gamma distribution linked to a logarithmic function. When significant, the factors under study will be compared by Bonferroni’s post-hoc test. Correlations will be described by the Pearson’s or Spearman’s test. The PASW18 (version 18.0, SPSS, Chicago, Illinois, USA) will be used in this analysis.

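### The protocol article requires effects to be controlled for exercise, co-interventions and treatment changes that arise after randomisation; as covariates these can bias the randomised comparison, and the stated GEE does not include them

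*Protocol article*

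**What the plan says.** Under Independent/exposure variables and confounding, the protocol article says that each treatment's effect on the outcomes "must be controlled for the confounders of concomitant physical exercise or co-intervention, and any changes regarding medications or non-pharmacological treatment". The wording is mandatory and covers all endpoints. It is not limited to baseline values or to a sensitivity analysis.

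Other sections bear on it:

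- **Timing.** Under Randomization, patients are allocated once the pre-intervention tests are finished, "in a 1:1:1 ratio using a pre-generated simple randomization list". Under Sociodemographic and clinical variables, "Any change in pharmacological management should also be reported and recorded in the study".
- **What patients are told.** Controls: "Patients will be oriented to keep their pharmacological routine and daily activities with no structured exercises". All patients: "Patients should be instructed to maintain their activities of daily living and eating routine, as established on the date of enrollment".
- **Openness.** Under Study design, those delivering the interventions are "blinded for outcomes, but not for groups".
- **Model.** Under Statistical analysis, the arms are compared by a GEE "in order to compare the effects (means) across the three groups and the two times, in addition to the group × time interaction". No covariates are named.

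**The concern.** In a randomised trial, a confounder of the effect of assignment would have to be a common cause of allocation and outcome. Exercise, co-interventions and treatment changes during the 8 weeks come after allocation, so they cannot be that. If the arm influences them, they may lie on the path from arm to outcome. Adjustment then removes that part of the effect. If they also share an unmeasured cause with PImax, adjustment opens a non-causal path between arm and outcome. Either way, the adjusted coefficient no longer estimates the effect of assignment.

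An analyst who follows the confounding section fits one model, and an analyst who follows the statistical section fits another. With 33 patients expected, the two can give visibly different primary results, and the article does not say which section governs.

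**Working it through.** **1. The two sections side by side.**

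| | Confounding section | Statistical analysis section |
|---|---|---|
| Terms | effects controlled for exercise, co-intervention, and medication or other treatment changes | group, time, group × time |
| Status | mandatory, all endpoints | the only model stated |
| Post-randomisation covariates | required, if read as analysis | none named |

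The model does not carry out the instruction.

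**2. Timing.** Randomisation follows the pre-intervention tests. Concomitant exercise and changes in treatment are events of follow-up, so the listed variables come after allocation.

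**3. When adjustment moves the estimate.** For a linear model with one post-treatment measurement per patient:

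adjusted estimate = unadjusted estimate − (difference in the covariate between arms) × (within-arm slope of the outcome on the covariate).

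The unadjusted contrast is unbiased for the effect of assignment. If the arm does not shift the covariate, the second term is zero in expectation and adjustment does no harm.

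**4. Illustrative sizes.** From Sample size: SD 12 cm H2O, planned difference 15 cm H2O. The shift and slope are assumptions; the document gives neither.

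| Shift between arms (SD) | Slope (SD per SD) | Change in estimate (SD) | × 12, in cm H2O |
|---|---|---|---|
| 0 | any | 0 | 0 |
| 0.4 | 0.2 | 0.08 | 1.0 |
| 0.4 | 0.3 | 0.12 | 1.4 |
| 0.8 | 0.2 | 0.16 | 1.9 |
| 0.8 | 0.3 | 0.24 | 2.9 |

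**5. Check by simulation** (400,000 records, two arms, direct effect 15, outcome SD about 12, all inputs assumed). The covariate is binary. Where the arm affects it, its prevalence is 30% in control and 60% in the treated arm.

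| Scenario | Unadjusted | Adjusted | Change |
|---|---|---|---|
| Arm does not affect covariate | 15.05 | 15.05 | 0 |
| Same, with an unmeasured common cause of covariate and outcome | 15.0 | 15.01 | 0 |
| Covariate a mediator worth 6 cm H2O | 16.9 | 15.08 | 1.8 |
| Covariate a collider, unmeasured common cause | 15.0 | 13.83 | 1.2 |
| Mediator and collider | 16.79 | 13.79 | 3.0 |

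The formula in step 3 agrees. For the mediator, 0.3 × 6 = 1.8, and the total effect is 15 + 1.8 = 16.8. The unadjusted estimate matches the effect of assignment in every scenario, within simulation error.

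**6. Scale.** With 11 per arm, the standard error of a two-arm difference is 12 × √(2/11) = 5.1 cm H2O. A shift of 3.0 is 3.0/5.1 = 0.6 standard errors and 3.0/15 = 20% of the planned difference.

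**7. A limit.** The size also depends on how the covariate enters. In the identity-link GEE with two times, an exchangeable correlation and complete data, a covariate entered only as a constant main effect leaves the group × time contrast unchanged. The shifts above apply when it is allowed to act on the post-test or on the change. The article does not say how it would enter.

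**The case against.** **Control may mean control by design.** The Discussion uses the word that way when it says that blinding controls performance bias. Patients are asked to keep their routines stable, and controls to do no structured exercise. This reading is possible. It fits the sentence poorly, however: the sentence stands under a confounding heading and speaks of controlling an effect on endpoints for confounders. Medication changes, moreover, are to be recorded, which is not the same as preventing them.

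**The stated model contains no such covariates.** If the statistical section governs, this adjustment bias does not occur. That is correct. A reader might infer that the planned primary comparison is biased, but the document does not support that. It shows two sections that disagree, one of which would permit a biased analysis.

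**A separate analysis plan may settle it.** It may. The point is not a missing detail: the sentence states a wrong requirement, and a plan that followed it would inherit the error.

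**Adjustment need not bias.** This also stands. A reader might conclude that the listed variables are certainly mediators or colliders, but some drug changes may have nothing to do with the arm. The active arm is described as "Active protocol with yoga body movements". Those movements are the assigned treatment and not concomitant exercise, so they do not by themselves show that allocation shifts the covariate. Influence of the arm is plausible because treatment is open, but it is not demonstrated.

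**Conclusion.** The point holds in a limited form. The confounding section mislabels post-randomisation events as confounders and requires control for them. Done as covariate adjustment, this can bias the estimate of the effect of assignment. It also conflicts with the stated GEE. The logic rests on the article's own order of events; whether bias would arise depends on the arm affecting these variables, which the document does not establish.

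The size is unknown. The range of 0 to about 3 cm H2O comes wholly from assumed inputs, and even its upper end is only about 0.6 standard errors at 11 per arm. It should not be cited as the bias of this trial. Nor does the point imply that the primary model must add baseline PImax or centre: baseline is already one of the two modelled times, and the article states no stratification by centre.

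**What to change.** Replace the sentence in the confounding section with text to this effect: the primary comparison is by assigned arm, using the GEE in the Statistical analysis section without covariates that arise after randomisation; recorded exercise, co-interventions and changes in medication or other treatment are described by arm; any model that includes them is exploratory and labelled as not estimating the effect of assignment.

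The cost is one sentence in the protocol and the matching line in any analysis plan. The primary model does not change. The description by arm uses what is recorded. Recording of medication changes is stated; follow-up recording of exercise and co-interventions is not described in the article, so the sponsor should confirm what is held. With 20 patients enrolled and 18 completed at publication, out of 33 expected, the change could be made before the final analysis.

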### Statistical analysis

Initially, a descriptive analysis will be performed and data will be expressed as absolute and relative frequency, besides mean and standard deviation or quartiles, accordingly. The treatment groups will be compared using the generalized estimating equation, specific for repeated measurements, in order to compare the effects (means) across the three groups and the two times, in addition to the group × time interaction. The generalized estimating equation matrix of robust estimator covariance and exchangeable work correlation matrix will be used if normal distribution is found and will be analyzed by an identity binding function. In contrast, if an asymmetrical distribution is found, data will be analyzed using a gamma distribution linked to a logarithmic function. When significant, the factors under study will be compared by Bonferroni’s post-hoc test. Correlations will be described by the Pearson’s or Spearman’s test. The PASW18 (version 18.0, SPSS, Chicago, Illinois, USA) will be used in this analysis.

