**Methods/design:**

A PROBE (prospective randomized open blinded end-point) parallel-group trial will be conducted at two specialized HF clinics. Adult patients previously diagnosed with HFpEF will be included. After signing informed consent and performing a pre-test intervention, patients will be randomized into three groups and provided with either (1) active yoga breathing techniques; (2) passive yoga breathing techniques (pranayama); or and (3) control (standard pharmacological treatment). Follow-up will last 8 weeks (16 sessions). The post-intervention tests will be performed at the end of the intervention period for analysis of outcomes. Interventions will occur continuously according to patients’ enrollment. The main outcome is respiratory muscular resistance. A total of 33 enrolled patients are expected. The present protocol followed the SPIRIT guidelines and fulfilled the SPIRIT checklist.

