### Sample size

For sample size calculation, the higher the effect size and lower standard deviation in relation to the effect, the lower the sample size required to confirm the result. Thus, based on previous studies, the sample size was calculated using inspiratory muscle pressure as endpoint [18]. Considering a difference among treatments (effect size) of 15 cm H_2_O and a standard deviation (SD) of 12 cm H_2_O in the PI_max_, representing a 1.2 ratio (effect size/SD), using an α = 0.05 and power of 80%, nine patients would have to be included per group. In addition, considering a potential loss in patient follow-up of between 10% and 20%, the sample was set to 11 patients per group.

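### The GEE with robust covariance is specified for about 30 patients without a small-sample correction, a t/F reference or a decisive term; run in its usual Wald form, the 5% interaction test has a type I error of about 10-11%

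*Protocol article*

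**What the plan says.** The Statistical analysis section of the protocol article chooses a GEE for repeated measurements "in order to compare the effects (means) across the three groups and the two times, in addition to the group × time interaction". For normally distributed data it fixes the estimator and the link: "The generalized estimating equation matrix of robust estimator covariance and exchangeable work correlation matrix will be used if normal distribution is found", with an identity link. Otherwise, "if an asymmetrical distribution is found, data will be analyzed using a gamma distribution linked to a logarithmic function". Any factor found significant is then followed by Bonferroni comparisons, and the software is PASW 18. The section gives no test statistic, finite-sample correction or reference distribution. It does not say which of group, time and interaction decides the primary endpoint, PImax.

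The size of the trial is stated in the abstract ("A total of 33 enrolled patients are expected") and under Sample size: "using an α = 0.05 and power of 80%, nine patients would have to be included per group", and "considering a potential loss in patient follow-up of between 10% and 20%, the sample was set to 11 patients per group". Allocation is "in a 1:1:1 ratio using a pre-generated simple randomization list", so arm sizes may differ by chance.

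**The concern.** The sandwich estimator is justified as the number of independent clusters grows. With 9 to 11 patients per arm it has two defects. It understates the variance, because it is built from residuals that are too small. It is also usually referred to a chi-square or normal distribution, which ignores the uncertainty in the estimated variance. Both defects push towards rejection. The Bonferroni step uses the same understated standard errors and so cannot repair them.

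The section also leaves room for choice. The group main effect averages the pre-treatment and post-treatment values, so a 15 cm H2O effect at week 8 appears in it as 7.5. The time effect is not a randomised comparison. Only group by time compares the change in PImax between arms, yet it is listed alongside the other two. Finally, the scale of the effect (difference or ratio) depends on the distribution seen in about 30 patients.

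At stake is whether a positive PImax result carries the 5% false-positive risk that the reader will assume.

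**Working it through.** **Inputs.** Alpha 0.05, 9 per group needed and 11 per group enrolled (Sample size); 33 in total (abstract); three arms, two times, robust covariance, exchangeable correlation (Statistical analysis); simple 1:1:1 list (Randomization). The stated loss of 10-20% leaves 11 × 0.9 = 9.9 to 11 × 0.8 = 8.8 per arm.

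**The plan's own figure.** n per group = 2(z_alpha + z_beta)² / ratio². With the printed ratio of 1.2 and one-sided alpha, 2(1.645 + 0.842)² / 1.44 = 8.6, so 9. A two-sided calculation gives 10.9, so 11. At 15/12 = 1.25 the values are 7.9 (8) and 10.05 (11). Nine is therefore matched by a one-sided calculation. That is a separate matter; here only the arm sizes are needed. Inflation for 15% loss: 9/0.85 = 10.6, so 11.

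**The variance.** With two times and complete data, group by time compares mean changes. The uncorrected robust variance of an arm's mean change is SS/n², where SS is the sum of squared deviations of change within the arm. The unbiased value is SS/[n(n−1)]. The ratio is (n−1)/n: 8/9 = 0.89 at 9 per arm and 10/11 = 0.91 at 11.

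**One pairwise contrast (exact for equal arms, normal data, equal variances).** The Wald z equals the two-sample t multiplied by √[n/(n−1)]. Rejecting at |z| > 1.96 means rejecting at |t| > 1.96√[(n−1)/n].
- n = 9: |t| > 1.848 on 16 df, probability 8.3%.
- n = 11: |t| > 1.869 on 20 df, probability 7.6%.

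**The 2-df interaction test (simulated under the null).** The Wald statistic is referred to chi-square with 2 df (critical value 5.991).

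| Setting | Type I error |
|---|---|
| 9 / 10 / 11 per arm, closed form, normal data | 10.8% / 10.3% / 9.6% |
| Full GEE fits, 9 / 10 / 11 per arm (3,000 runs each) | 10.2% / 10.0% / 9.6% |
| Full GEE fits, 11 per arm with 15% dropout | 10.7% |
| Gamma/log GEE, 10 per arm (1,500 runs) | 10.5% |
| Averaged over simple randomization, N = 27 / 30 / 33 | 12.2% / 11.2% / 10.4% |

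Independent repeats of the closed-form simulation gave 10.8-11.0%, 10.2-10.3% and 9.6-9.7% at 9, 10 and 11 per arm.

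**After Bonferroni.** With equal arms, a false pairwise claim occurs in 8.5-9.5% of null trials, or 8.2-9.5% if a significant omnibus test is required first. Averaged over simple randomization, the figure with the omnibus requirement is 9.0% (N = 33) to 10.5% (N = 27).

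**What repairs it (11 per arm).** Uncorrected sandwich with chi-square: 9.6%. F reference alone: 7.7%. Leverage-corrected (Mancl-DeRouen) sandwich alone, still with chi-square: 6.2%. Both together, with F(2, N−3): 4.8%. At 27 and 30 patients both together give 4.8% and 4.9%. ANOVA on the change score gives 4.9-5.2%. Correction and reference distribution are both needed.

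**The case against.** The strongest objection is that the section says neither Wald nor uncorrected. A reader might infer that the trial's true type I error is 10%; the document does not support that. A generalized score test on the same data gives 4.3-4.6%, and a corrected sandwich with an F reference gives 4.8-4.9%. Both are compatible with the words robust estimator. The test statistic is also a detail that an article may leave to an analysis plan. This stands as a limit on certainty. It does not remove the point: the section fixes estimator, working correlation, link, post-hoc method and software, and the combination it fixes roughly doubles the error in its ordinary form.

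Second, a reader might count group and interaction together and conclude that the false-positive risk is about 20%. That would be wrong as evidence against the sandwich. Exact F-tests on the same two terms already give 9.7-9.8%, so about half is plain multiplicity. The section also does not say that a significant group main effect would be claimed as efficacy.

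Third, group by time in a two-time GEE validly estimates the difference in change, so ANCOVA is a gain in efficiency and not the correction of an error. That also stands. The size of the gain depends on the correlation between baseline and week 8, which the document does not give, and on whether the SD of 12 refers to patients or to changes, which it does not say.

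Fourth, the Study design section blinds the analysts, so the choice of link is unlikely to be steered by a known treatment effect. That lowers the risk of bias. It does not change the fact that the estimand moves from a difference to a ratio depending on the data.

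**Conclusion.** The concern holds in conditional form. The plan pairs a large-sample covariance estimator with 27 to 33 patients and names no correction, no t/F reference and no decisive term. Run as an uncorrected Wald chi-square test, the nominal 5% group-by-time test has a type I error of about 10-11% with equal arms and about 10-12% averaged over simple randomization. False pairwise claims after Bonferroni occur in about 8-9.5% with equal arms. A single unadjusted contrast is inflated less, to about 8%.

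These figures assume normal data with equal variances and mostly complete follow-up. The checks with dropout and with the gamma model gave similar values. That the uncorrected Wald form will be used is an inference from what the section names and leaves out; the actual error could be near 5% if a score test or a corrected test is intended. The plan should say which.

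**What to change.** Name the between-arm comparison of change in resting PImax (group by time) as the only primary treatment test, and analyse it in one of two ways:

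1. ANCOVA of week-8 resting PImax on arm and baseline PImax, with a t/F reference.
2. The GEE as planned, with a small-sample-corrected sandwich and a t/F reference.

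Follow either with the three Bonferroni-adjusted pairwise contrasts. Fix the identity link for PImax in advance, so that the result is in cm H2O, and keep the gamma/log model as a sensitivity analysis.

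**Cost.** This changes analysis wording only and needs no new data; baseline PImax is already collected. The p-values become slightly larger. Whether PASW 18 offers the corrected sandwich has to be checked; ANCOVA needs only standard software, but leaves out patients without a post-test. The control for co-intervention and medication change required under Independent/exposure variables and confounding is untouched by either route and has to be specified separately. The Trial status section reports 20 enrolled and 18 completed, so at that stage the change could still be made before the planned sample was complete.

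### The robust (sandwich) GEE is prescribed without a small-sample correction for 9 to 11 patients per arm, so the nominal 5% group × time test on PImax rejects about 9.6–11% of the time under the null

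*Protocol article*

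**What the plan says.** The Statistical analysis section compares three groups at two times, with a group × time interaction, by generalized estimating equations. For normally distributed outcomes it fixes the covariance and the working correlation: "The generalized estimating equation matrix of robust estimator covariance and exchangeable work correlation matrix will be used if normal distribution is found". Skewed outcomes go to a gamma model with a log link. Significant factors are followed by Bonferroni comparisons. On software it says: "The PASW18 (version 18.0, SPSS, Chicago, Illinois, USA) will be used in this analysis". It mentions no finite-sample correction and no t or F reference.

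The Sample size section bases the trial on PImax, with a "difference among treatments (effect size) of 15 cm H_2_O and a standard deviation (SD) of 12 cm H_2_O in the PI_max". It concludes: "using an α = 0.05 and power of 80%, nine patients would have to be included per group". It then allows for loss: "considering a potential loss in patient follow-up of between 10% and 20%, the sample was set to 11 patients per group". The abstract gives the total: "A total of 33 enrolled patients are expected". Allocation is "in a 1:1:1 ratio using a pre-generated simple randomization list". The Endpoints section makes PImax primary.

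**The concern.** The sandwich estimator is justified by a large number of independent clusters. Here the clusters are patients, and each arm's variance rests on about nine to 11 of them. Two errors then act in the same direction. The robust variance is biased downwards, and the usual Wald test refers the statistic to a normal or chi-square distribution as if that variance were known. Both make p-values too small and intervals too narrow.

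The sizing at α = 0.05 and the Bonferroni step both take for granted that each test holds its level. If it does not, a positive PImax result carries more false-positive risk than stated. Bonferroni cannot repair this, because each comparison it adjusts is already oversized.

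**Working it through.** **Inputs.** From the Sample size section: nine evaluable and 11 enrolled per arm, difference 15 cm H₂O, SD 12 cm H₂O, α = 0.05, power 80%. From Statistical analysis: three groups, two times, robust covariance, exchangeable working correlation. My assumptions: normal data, no true effect, equal arms and complete pairs unless stated, and a Wald chi-square test.

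**The plan's own figure.** The ratio is 15/12 = 1.25 (the text gives 1.2). A one-sided two-sample t test at 1.25 needs 8.7, that is nine per group. A two-sided t test needs 11.1, that is 12. Nine is therefore reproducible, though only as a one-sided figure. That is a separate matter. For loss, 9/(1 − 0.18) = 10.98, so 11 fits a loss inside 10–20%. The relevant range is nine to 11 per arm.

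**Reduction.** With two times, complete pairs and a group × time term, the GEE contrast is the difference between arms in mean change d. The robust variance of an arm's mean change is

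v = Σ(d − d̄)² / n²,

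which is (n − 1)/n times the unbiased value: 8/9 = 0.889 at nine and 10/11 = 0.909 at 11. The rejection rates depend neither on the SD nor on the pre–post correlation.

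**Pairwise test, exact.** Size = P(|t| > 1.96 × √((n − 1)/n)) with 2n − 2 degrees of freedom.
- n = 9: 1.96 × √(8/9) = 1.848; P(|t₁₆| > 1.848) = 0.083.
- n = 11: 1.96 × √(10/11) = 1.869; P(|t₂₀| > 1.869) = 0.076.

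**Interval width relative to the t interval.**
- n = 9: 1.848/2.120 = 0.87, so the t interval is 1/0.87 = 1.15 times as wide.
- n = 11: 1.869/2.086 = 0.90, so the t interval is 2.086/1.869 = 1.12 times as wide.

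**Bonferroni.** For three pairs the normal critical value is 2.394. At n = 9 each pair has size P(|t₁₆| > 2.394 × √(8/9)) = 0.038, against the intended 0.05/3 = 0.017.

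**Global test.** W = Σ (d̄ − μ̂)²/v over the three arms, where μ̂ is the inverse-variance weighted mean. W is compared with the chi-square value on 2 df, 5.99. The F version compares W/2 with F(2, 3n − 3). Each entry for a global test or the Bonferroni family rests on at least 200,000 simulated null trials.

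| Under the null | 9 per arm | 11 per arm |
|---|---|---|
| Group × time, robust, chi-square | 10.9% | 9.6–9.7% |
| Group × time, robust uncorrected, F | 8.3% | 7.7% |
| Pairwise at 5%, robust, normal | 8.3% | 7.6% |
| Any of three Bonferroni pairs | 9.6% | 8.4% |
| Coverage of nominal 95% interval | 91.7% | 92.4% |
| Kauermann-Carroll sandwich, F | 6.4% | 6.2% |
| Mancl-DeRouen sandwich, F | 4.8% | 4.9% |
| Linear model on change, F | 5.0% | 5.0% |

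Ten per arm gives 10.1–10.2% for the first row. Requiring both a significant global test and at least one Bonferroni pair still gives 9.3% and 8.2%.

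**Direct GEE fits** (exchangeable, robust, 3,000 runs each, Monte Carlo SE about 0.55 points): 10.4% at nine per arm, 9.4% at 11, and 11.0% with 11 enrolled and 15% random loss of the post-test.

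**Comparisons.** At 30 per arm the robust chi-square test rejects 6.5%. A model-based covariance with a chi-square reference would reject 6.5–6.9% at nine to 11 per arm, so most of the excess comes from choosing the robust estimator. Uneven arms of 6, 9 and 12, which a simple list could produce, give 12.0%.

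**The case against.** The strongest objection is that the article never says the sandwich is uncorrected, and names neither a test statistic nor a reference distribution. It is a condensed account, and a full analysis plan could supply a correction. The name of the software settles nothing, because the document does not say which options will be used. This limits certainty about what will be run. It does not remove the point: the article positively chooses the robust estimator for arms of this size, and the uncorrected form still rejects about 7.7–8.3% with an F reference. The excess therefore does not depend only on the unstated reference distribution.

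Other objections concern reach, and they stand.
- A reader might infer that every secondary test runs at twice its level. NYHA class is ordinal and the normal and gamma branches do not describe its analysis. The correlations use Pearson or Spearman tests, with no sandwich variance. Pairwise tests run at about 1.5–1.7 times nominal; only the global test is near double.
- A reader might infer a 10–11% chance of wrongly claiming that yoga raises PImax. The global test also counts harm and differences between the two yoga arms. With three Bonferroni contrasts after a significant global test, a false claim that either yoga arm beats control arises in 3.4% of null trials at nine per arm and 3.0% at 11, against about 1.5% for an ANOVA version. The ratio is still about two, but the absolute risk is lower.
- A reader might carry the calculation to still smaller arms throughout. Simple randomization can leave one arm small, but with 33 enrolled and nine evaluable per arm planned, three arms of six is not this trial.

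**Conclusion.** The concern holds for PImax and the other continuous endpoints analysed by this GEE. As written, with the usual Wald chi-square test, the nominal 5% group × time test has a true size of about 9.6–11% at nine to 11 patients per arm. Pairwise 5% tests run at about 7.6–8.3%, the Bonferroni family at about 8.4–9.6%, and nominal 95% intervals cover about 92%. Point estimates are not affected.

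The figures assume normal changes, and equal arms with complete pairs except where stated. Random loss or uneven arms gave similar or larger errors. For the gamma/log branch, one set of 2,500 fits rejected 9.9%. That gives no sign that the branch escapes the problem, but the conclusion does not rest on it.

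**What to change.** For PImax and the other continuous endpoints in this GEE, replace the robust-GEE test by a linear model, or a mixed model with Satterthwaite or Kenward-Roger degrees of freedom, using F and t reference distributions. The linear-model F test held 4.9–5.0% at every arm size tried, including 6/9/12. Base all pairwise p-values and intervals on t.

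If GEE is kept, specify the Mancl-DeRouen corrected sandwich with F and t degrees of freedom based on the number of patients; this gives about 4.8–4.9% with equal arms. Kauermann-Carroll is not enough here, since it leaves about 6.2–6.4% on the global test even against F.

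The cost is one sentence in the analysis section and a different procedure call, with no new data. Intervals become about 12–15% wider, which is their correct width. The Trial status section reports 20 patients enrolled and 18 completed, so the change should be recorded before any comparison by group.
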